## Abstract

**Background:**

Ultrasonography (US) is widely used as a standard surveillance tool for patients who are at a high risk of having hepatocellular carcinoma (HCC); however, conventional B-mode US appears to be insufficient in order to ensure the early detection of HCC. Perfluorobutane allows very stable Kupffer phase imaging for at least 60 min, which is tolerable for examinations of the entire liver. The purpose of our study is to evaluate the added value of contrast-enhanced US using perfluorobutane to that of conventional B-mode US as an HCC surveillance tool for patients with liver cirrhosis.

**Methods/Design:**

SCAN (Sonazoid-US for surveillance of hepatoCellulArcarciNoma) is a prospective, multi-institutional, diagnostic trial using an intra-individual comparison design in a single arm of patients. This study was approved by our five institutional review board and informed consent was obtained from all participating. We obtained consent for publication of these data (contrast enhanced US images, CT or MRI images, laboratory findings, age, sex) from all participating patients. All patients will undergo conventional B-mode US immediately followed by contrast-enhanced US. The standardized case report forms will be completed by operating radiologists after B-mode US and contrast-enhanced US, respectively. If any lesion(s) is detected, the likelihood of HCC will be recorded. The primary endpoints are a detection rate of early-stage HCC and a false referral rate of HCC. Intra-individual comparison using Mcnemar’s test will be performed between B-mode US and contrast-enhanced US. The study will include 523 patients under HCC surveillance in five medical institutions in Korea.

**Discussion:**

SCAN is the first study to investigate the efficacy of contrast-enhanced US in surveillance using two reciprocal endpoints specialized for the evaluation of a surveillance test. SCAN will provide evidence regarding whether patients can truly benefit from contrast-enhanced US in terms of the detection of early stage HCC while avoiding additional unnecessary examinations. In addition to the study protocol, we elaborate on potentially debatable components of SCAN, including the design of an intra-individual comparison study, study endpoints, composite reference standards, and indefinite imaging criteria regarding the likelihood of HCC.

## Background

Currently, clinical practice guidelines recommend semiannual surveillance for patients who are at a high risk of having hepatocellular carcinoma (HCC) [1–4]. While ultrasonography (US) has been used as a standard examination for HCC surveillance [5], the reported sensitivities, varying from 59% to 92% [6], appear to be insufficient to ensure the early detection of HCC. Using US contrast agents, attempts have been made to improve the efficacy of US in diagnosing HCC; however, US contrast agents in surveillance settings have only rarely been validated [6].

Perfluorobutane (Sonazoid; GE Healthcare, Oslo, Norway) is a second-generation US contrast agent, which has unique characteristics allowing Kupffer phase imaging. Kupffer cells, liver-specific macrophages, phagocytize the perfluorobutane [7] and amplify the ultrasound scattering in order to generate the amplified sound wave. Therefore, a hepatic lesion in which the number of Kupffer cells are either markedly decreased or absent shows a defect on US during the Kupffer phase. Perfluorobutane has been studied for various applications such as the diagnosis of focal liver lesions [8–13], grading of the histologic differentiation of HCCs [14, 15], and guidance of surgical or radiological interventions [16–19].

As the Kupffer phase lasts at least 60 minutes with high stability and allows sufficient time to examine the entire liver, we have noted the value of perfluorobutane as a surveillance tool. One earlier, brief report showed that there was improvement in the detection of small HCCs using perfluorobutane [9]. However, it is still unclear whether patients truly benefit from contrast-enhanced US in terms of the detection of early-stage HCC while avoiding unnecessary additional examinations. The purpose of this study is to investigate the added value of contrast-enhanced US to conventional B-mode US as an HCC surveillance tool in patients with liver cirrhosis.

## Method/design

### Design

Sonazoid-US for surveillance of hepatoCellulArcarciNoma (SCAN) is a prospective, multi-institution, diagnostic trial using an intra-individual comparison design in a single-arm of patients. The primary endpoints are a detection rate of early-stage HCC and a false referral rate. Our study will include 523patientsunder HCC surveillance at five medical institutions (Seoul National University Bundang Hospital, Seoul National University College of Medicine, Severance Hospital, Yonsei University College of Medicine, University of Ulsan College of Medicine, Asan Medical Center, Samsung Medical Center, Sungkyunkwan University School of Medicine, Seoul National University Hospital) in Korea. The institutions were chosen based on their potential to recruit a high number of patients currently in HCC surveillance. The SCAN protocol and the informed consent form have been approved by the ethics committee of each participating institution. Recruitment commenced in October 2014. The date of trial registration (ClincalTrials.gov: NCT02188901) in this study is July 3, 2014. The last patient enrolled in August 30, 2016 and follow up to see the primary end point is still ongoing. All authors have no other relationships/conditions/circumstances that present a potential conflict of interest of relationships.

### Eligibility criteria

Patients aged 20 to 80 years, having liver cirrhosis related to HBV, HCV or primary biliary cirrhosis, and undergoing US for HCC surveillance are eligible for the study. Liver cirrhosis is defined as having one of following criteria [20]: (a) histologically proven liver cirrhosis (METAVIR score 4); (b) endoscopically or radiologically identified esophageal or gastric varices; (c) hepatic surface nodularity seen on a previous cross-sectional imaging study such as US, computed tomography or magnetic resonance imaging; (d)serum platelet count <100,000 /mm^3^; (e) serum albumin <3.5 g/dL; and (f) prothrombin time–international normalized ratio (PT-INR)>1.3. Patients are not eligible for the study if they have history of HCC (either treated or not treated) or a contraindication for the perfluorobutane.

### US technique

All patients will undergo contrast-enhanced US (Kupffer-phase US ± vascular-phase US) immediately following conventional B-mode US lying in the supine and/or left lateral decubitus position. One of the fellowship-trained abdominal radiologists in each participating institution, and who is aware of the patient’s previous clinical and radiological information, performs B-mode US using an ultrasound system (LOGIQ E9, GE Healthcare, Milwaukee, WI, USA) equipped with a convex transducer operating at a frequency of 1 to 6 megahertz. 16 μg of perfluorobutane is dissolved in 2 mL of sterile water, and the solution is intravenously administrated as a bolus at a dose of 0.015 mL/kg body weight, immediately followed by a 10-mL normal saline flush via the antecubital vein. Ten to 15 minutes after the perfluorobutane administration, the same radiologist performs contrast-enhanced US during the Kupffer-phase with the same ultrasound system. If a new lesion is detected on the preceding B-mode US, vascular-phase US will be performed for the target lesion before the Kupffer- phase and during the arterial (10-40 seconds after administration of perfluorobutane), portal venous (60-90 seconds), and delay (3 minutes)phases. If a new lesion is detected only o n Kupffer-phase US, vascular-phase US will be performed for detecting the target lesion after the Kupffer- phase with re-administration of the same dose of perfluorobutane [9] (Fig. 1). All phases are to be recorded as movie clips. Some representative images, especially in the arterial and Kupffer- phases, are obtained and sent to a picture archiving and communications system (PACS).If there are two or more lesions in a single patient, vascular-phase US will be performed for the largest lesion. In performing US, the radiologists follow the guidelines of the Korean Society of Ultrasound in Medicine [21]. Otherwise, there are no specific restrictions regarding the US technique or time constraint. The scanning parameters are detailed in Table 1.

**Fig. 1 Fig1:**
[figure not shown]
Study flow diagram*After re-administration of perfluorobutane.*CT* computed tomography, *HCC* hepatocellular carcinoma, *MRI* magnetic resonance imaging, *US* ultrasonography

**Table 1 Tab1:** Contrast-enhanced US performed according to theperfluorobutane(Sonazoid) protocol

Imaging protocol	
Intravenous access	Antecubital or forearm
Contrast preparation	16 μg of perfluorobutane dissolved in 2 mL of sterile water
Injection dose	0.015 mL/kg body weight
Injection method	Bolus with 10-mL normal saline flush
Contrast US setting	
Scanning view	Dual view ( B-mode + contrast mode)
Mechanical index	0.20 -0.26
Dynamic range	60 - 65dB
Location of the beam focus	Posterior margin of the liver
Contrast harmonic imaging	Used
Kupffer phase	10 to 15 minutes after the injection of perfluorobutane
Vascular phase	After reinjection of perfluorobutane
Artery phase	10-40 seconds
Portal phase	60-90 seconds
Delay phase	3–4 minutes

### Image interpretation

The standardized case report forms will be completed by the operating radiologist after completion of B-mode US and contrast-enhanced US respectively, and will include the subjective quality of the US examination (acceptable or incomplete), the presence or absence of a lesion, and the presence of portal-venous thrombosis. If any lesion(s) is detected, the number, size, location according to Couinaud’s classification, sonographic features, enhancement pattern, and the likelihood of HCC (using a 3-point Likert scale: benign, probably benign, and suspicious HCC) of the lesion(s) are also to be recorded. The imaging criteria for the likelihood of HCC are not protocolled, and the judgement for the likelihood of HCC will be left to the discretion of the radiologists.

### Further imaging work-up

If a patient has any lesion(s) of which the likelihood of HCC is grade 3 (suspicious HCC) on either B-mode US or contrast-enhanced US, the patient will undergo CT or MRI for further characterization of the lesion(s) within 60 days after the surveillance US. For patients in whom no lesion is identified or in those with a lesion in which there is a likelihood of HCC ≤ grade 2 on both B-mode US and contrast-enhanced US, follow-up imaging will be recommended according to the standard surveillance program of each participating institution.

### Reference standards

For patients undergoing hepatic surgery or biopsy, the final diagnosis will be determined based on the pathological HCC criteria as follows [22]. (a) The hepatocellular origin of the tumor verified by architectural and cytological evidence of hepatocellular differentiation. (b) The presence of malignant features such as nuclear atypia and architectural alteration. Three immunohistochemical markers including glypican 3, heat shock protein 70, and glutamine synthetase are used for differentiating between the high-grade dysplastic nodule and well-differentiated HCC. If tumor cells are positive for two or three markers, the tumor will be diagnosed as well-differentiated HCC. For patients who do not undergo surgery or biopsy, the radiology expert panel in the central review unit will determine the final diagnosis using CT or MRI based on the Liver Imaging Reporting and Data System (LI-RADS) version 2014 [23, 24]. Image findings compatible with LR-4, LR-5 and LR5V will be diagnosed as HCC. The expert panel consists of radiologists who are not involved in the prospective US examination. They will be aware of the study concept and design, although they will be blinded to the details of the US results. As all analyses in SCAN will be performed in a per-patient manner, there will be no additional process which determines if a lesion identified on CT or MRI matches the lesion identified on the surveillance US.

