### Primary endpoints

The primary study endpoints are a detection rate of early-stage HCC and a false referral rate. The detection rate of early-stage HCC is defined as the proportion of patients having both positive US results and confirmed as having early-stage HCCs on reference standard procedures out of all patients enrolled in the study. The early-stage HCC is defined as a single HCC<5cm or up to three HCCs, each of which is less than 3 cm based on the Barcelona Clinic Liver Cancer staging system (BCLC stage 0 or A) [25]. The false referral rate is defined as the proportion of patients having positive US results but confirmed as not having HCC on reference standard procedures out of all patients enrolled in the study.

The likelihood of HCC = grade 3 will be regarded as test positive both for B-mode US and contrast-enhanced US. If a patient has two or more lesions, the lesion assigned the greatest likelihood of HCC will be regarded as the representative lesion of that patient. As patients who have positive results either on B-mode US or on contrast-enhanced US subsequently undergo reference standard procedures, the true-positives and false referrals are to be determined by comparing the case report forms of each US method with the reference standards. For example, if a patient has a lesion of which the likelihood of HCC is grade 3 on B-mode US but is grade 2 on contrast-enhanced US, and if the patient is finally confirmed as not having HCC on reference standard procedures, it will be counted as a false referral of B-mode US but not of contrast-enhanced US.

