### Composite reference standards

We set composite reference standards in SCAN, which uses either histopathology or radiology as the final diagnosis of HCC. Various treatments, such as surgery, radiofrequency ablation, percutaneous ethanol injection, and combined therapy of radiofrequency ablation and trans-arterial chemoembolization, are currently available for early-stage HCCs [1, 2, 31]. This makes the investigation of the efficacy of a diagnostic test for HCC more complex as histopathology, which has traditionally been used as the reference standard for imaging diagnosis, is not available in most patients. Furthermore, the very high specificity of the typical radiological features of HCC in an at-risk population rendered the imaging diagnosis a substitute for histopathology, and the recently updated American Association for the Study of Liver Diseases (AASLD) guidelines have even proposed that one imaging technique (either CT or MRI) showing the typical radiological features suffices for diagnosing HCC [2]. It is now regarded as unethical to perform a biopsy on a patient with HCC, in whom the biopsy is unnecessary for clinical purposes. If we use only histopathology as the reference standard, it should result in a significant bias as then only HCCs showing atypical radiological features will be included as true HCCs.

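### LR-4 without histology counts as confirmed HCC, a category the plan's rationale does not address; with about 9 discordant patients expected, a strict re-run should be prespecified

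*Protocol article*

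**What the plan says.** The section Reference standards sets two routes to the final diagnosis. Patients with surgery or biopsy are classified by pathology, with three immunohistochemical markers to separate high-grade dysplastic nodules from well-differentiated HCC. The rest go to imaging: "For patients who do not undergo surgery or biopsy, the radiology expert panel in the central review unit will determine the final diagnosis", using LI-RADS version 2014. The rule is: "Image findings compatible with LR-4, LR-5 and LR5V will be diagnosed as HCC". No further confirmation of an LR-4 reading is described. The panel did not perform the ultrasound and is blinded to its details.

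The Discussion, under Composite reference standards, defends the imaging route by saying that "the very high specificity of the typical radiological features of HCC in an at-risk population rendered the imaging diagnosis a substitute for histopathology". LR-4 is not mentioned there.

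The section Primary endpoints uses this diagnosis twice. Detection requires a positive ultrasound and confirmed early-stage HCC. False referral is "the proportion of patients having positive US results but confirmed as not having HCC on reference standard procedures", out of all patients enrolled. The Discussion, under Study endpoints, adds that a detection gain is worth having only if false referrals fall or hold steady.

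**The concern.** The article's rationale concerns lesions with the typical pattern. The rule it fixes also takes in LR-4, which LI-RADS grades separately from LR-5. The article does not define the categories; I assume only that LR-4 is the less certain of the two. On that assumption the reasoning offered does not reach the whole rule.

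The two primary endpoints are meant to check each other: more detections should not be bought with more false referrals. A generous call on an LR-4 lesion improves both at once for the exam that was positive. An error in the reference standard would then look like a gain on one endpoint and no harm on the other.

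**Working it through.** **Inputs (section Sample size).** Detection of early-stage HCC is 3.15% on B-mode (5% × 63%) and 4.75% on contrast-enhanced US (5% × 95%). Total discordance is 1.7%, of which 0.05% is B-mode only, so contrast-only is 1.7% − 0.05% = 1.65%. Difference: 1.65% − 0.05% = 1.60%, which equals 4.75% − 3.15%. Power is 80% and α is 0.05, with sidedness not stated.

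**Step 1: the plan's own figure.** With ψ = 0.017 (discordance) and d = 0.016 (difference):

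- Simple formula: N = (1.960 + 0.842)² × ψ / d² = 7.849 × 0.017 / 0.000256 = 521.2, so 522.
- Conditional-variance formula: N = (1.960√ψ + 0.842√(ψ − d²))² / d² = 518.9, so 519.
- Exact two-sided McNemar power at N = 523: 80.1%.

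The stated 523 reproduces as a two-sided calculation. It is not in dispute.

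**Step 2: how many patients carry the comparison.** Contrast-only: 523 × 0.0165 = 8.6. B-mode only: 523 × 0.0005 = 0.3. Together about 9.

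**Step 3: what one LR-4 reading does.** Take a patient without tissue, read as LR-4, within the early-stage limits and positive on one exam only.

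| Reading | Detection, positive exam | False referral, positive exam |
|---|---|---|
| LR-4 counted as HCC (plan) | +1 | 0 |
| LR-4 counted as not HCC | 0 | +1 |

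Each patient moves each rate by 1/523 = 0.19 percentage points. A patient positive on both exams moves both exams equally and drops out of McNemar's test.

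**Step 4: sensitivity of the test.** Exact two-sided p = 2 × P(X ≤ smaller count), X ~ Binomial(n discordant, 0.5).

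| Contrast-only v B-mode-only | Exact p |
|---|---|
| 9-0 | 0.004 |
| 8-0 | 0.008 |
| 7-0 | 0.016 |
| 6-0 | 0.031 |
| 5-0 | 0.0625 |
| 8-1 | 0.039 |
| 7-1 | 0.070 |

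From 9-0, three reclassifications leave p below 0.05 and a fourth does not. From 8-1 or 6-0, one is enough.

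The article does not say which form of McNemar's test will be used. With the uncorrected chi-square (critical value 3.84) the result is sturdier. 5-0 gives 25/5 = 5.0 and 7-1 gives 36/8 = 4.5, both still significant. It is lost at 6-1 (25/7 = 3.57) or 3-0 (9/3 = 3.0).

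**Step 5: range for the unknown share.** Let f be the share of discordant detections, in both directions, that no longer counts as HCC. The documents give no value for f; these are assumptions.

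| f | Exact power at N = 523 | N for 80% power (conditional-variance formula) |
|---|---|---|
| 0% | 80% | 519 |
| 10% | 73% | 577 |
| 20% | 63% | 649 |
| 30% | 51% | 742 |
| 40% | 38% | 866 |

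**The case against.** The rule is stated openly and in advance, it applies identically to both exams, and the panel is blinded to the ultrasound details. Pathology takes precedence wherever tissue exists. The article also argues, reasonably, that a histology-only standard would keep only radiologically atypical HCCs. All of this stands, and it makes LR-4 a defensible primary rule. It does not remove the concern: equal application cancels for patients positive on both exams but not for those positive on one, and the plan expects nearly all of these to be contrast-only.

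A stricter sensitivity run is often left to an analysis plan that is not shown here, so its absence alone would be no finding. The point rests on what the article does fix: a rule wider than the reason given for it, feeding both primary endpoints.

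It is also fair that counting every LR-4 without tissue as not HCC would turn some real HCCs into false referrals. An LR-4 reading does not confirm absence of HCC, which the endpoint definition requires. The remedy therefore has to report bounds.

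A reader might further infer that vein-invading tumours enter the early-stage endpoint, because LR5V is accepted as HCC and the listed criteria are size and number: "The early-stage HCC is defined as a single HCC<5cm or up to three HCCs, each of which is less than 3 cm". The documents do not support this. The same sentence continues "each of which is less than 3 cm based on the Barcelona Clinic Liver Cancer staging system (BCLC stage 0 or A", so the definition is tied to a stage. LR5V also has to be listed as HCC for the any-stage secondary endpoint, and so that such patients are not counted as false referrals. What remains is that the text does not say whether the stage or the size-and-number limits govern when they differ.

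**Conclusion.** The concern holds as a questionable design choice without a stated safeguard; it is not a contradiction. LR-4 without tissue becomes a final HCC diagnosis although the rationale does not address it, and each such patient positive on one exam only improves that exam on false referral and, if early-stage, on detection. With about 9 discordant patients expected, one to four reclassifications could change the conclusion under the exact test; the uncorrected chi-square would need more.

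This rests on the planning rates and on LR-4 being less certain than LR-5. The size of the effect is unknown, because the documents give neither the LR-4 share nor its accuracy. Losing four of nine detections is an illustration, not an estimate. Nor do the documents show that the rule is built to favour contrast-enhanced US: the shift goes to whichever exam alone was positive. The LR5V point is a wording clarification only.

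**What to change.** Keep the primary rule and prespecify a second run of both primary endpoints, using the LI-RADS categories the panel assigns anyway:

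1. **Detection.** Count as HCC only pathology-proven, LR-5 or LR5V cases, with early stage still defined by BCLC 0 or A.
2. **False referral.** Report two bounds: LR-4 without histology as HCC, and as not HCC.
3. **Claim.** State in advance that, if the runs disagree, the detection claim is limited to 'probable or definite HCC'.
4. **Reporting.** Give the number of LR-4 patients without histology, split by which exam was positive.

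As a minor clarification in Primary endpoints, state that BCLC stage 0 or A governs, so that LR5V counts in the any-stage endpoint only.

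The cost is a few sentences and one re-run, with no new patients or imaging. The article describes follow-up for the primary endpoint as ongoing, which leaves room to fix this before analysis. The downsides are fewer counted detections, hence less power, in the strict run, and an upper bound for false referrals that will include some true but unbiopsied HCCs.

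### An exam is credited with detecting early-stage HCC even if the lesion it flagged is not the HCC, because no lesion matching is planned

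*Protocol article*

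**What the plan says.** Three parts of the protocol article fix the rule.

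- **Reference standards.** HCC status comes from pathology or from a central panel reading CT or MRI, blinded to the US details. The section then says that "there will be no additional process which determines if a lesion identified on CT or MRI matches the lesion identified on the surveillance US". Its reason is that "all analyses in SCAN will be performed in a per-patient manner".
- **Primary endpoints.** The detection rate is "the proportion of patients having both positive US results and confirmed as having early-stage HCCs on reference standard procedures", out of all enrolled patients. Grade 3 is test positive for either exam. With several lesions, "the lesion assigned the greatest likelihood of HCC will be regarded as the representative lesion of that patient". Nothing compares the site of that lesion with the site of the reference HCC.
- **Image interpretation.** After each exam the operator records "the number, size, location according to Couinaud" segment, together with the likelihood grade. The data needed for matching are therefore collected separately for B-mode and for contrast-enhanced US.

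Secondary endpoints define the any-stage detection rate in the same way. No section of the article plans a lesion-matched analysis.

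**The concern.** Detection is scored from two facts that need not refer to the same lesion: a grade 3 call somewhere in the liver, and an HCC somewhere in the liver. Suppose B-mode flags a benign nodule while contrast-enhanced US flags the tumour in another segment. Both exams score a detection, and the pair becomes concordant. That patient is exactly the kind of evidence the trial seeks, and McNemar's test ignores concordant pairs.

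Such cases are plausible. All patients have cirrhosis, and the article leaves the criteria for grade 3 to the radiologist's discretion.

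The reason given does not lead to the rule. The patient can remain the unit of analysis while a detection still requires that the flagged lesion be the tumour. The sample size also takes the detection rates from sensitivities of 63% and 95%, which are naturally read as finding the tumour itself.

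What is at stake is the size and power of the comparison that carries the claim of added value. It rests on about nine discordant patients, so small numbers count.

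**Working it through.** **Inputs (Sample size section).** HCC prevalence 5%; detection 3.15% on B-mode and 4.75% on contrast-enhanced US; discordance 1.7%, of which 0.05% is B-mode only; N = 523; power 80%; α = 0.05 (sidedness not stated).

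**Cells implied by these inputs**
- Contrast only: 1.70 − 0.05 = 1.65%
- Both: 3.15 − 0.05 = 3.10%
- Neither, among HCC patients: 5.00 − 3.10 − 1.65 − 0.05 = 0.20%
- Difference: 1.65 − 0.05 = 1.60 points

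**Reproducing the plan.** Power of the exact two-sided McNemar test is the sum over k of P(K = k) × P(reject | k). Here K ~ Binomial(523, 0.017), and the split of k pairs is Binomial(k, 0.0165/0.017). The result is 80.1%, and 523 is the smallest N that reaches 80%. The plan's figure is reproduced.

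**Expected counts at N = 523**
- Contrast-only pairs: 523 × 0.0165 = 8.6
- B-mode-only pairs: 523 × 0.0005 = 0.3
- All discordant pairs: 523 × 0.017 = 8.9
- HCC patients missed by B-mode: 523 × (0.05 − 0.0315) = 9.7
- HCC patients missed by contrast-enhanced US: 523 × (0.05 − 0.0475) = 1.3

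Only the patients in the last two lines are open to false credit.

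**Effect of not matching, simple model.** The documents give no rate, so q is an assumption: the share of contrast-only detections that also carry an unrelated B-mode grade 3 lesion. The contrast-only cell becomes 0.0165(1 − q); the B-mode-only cell stays at 0.0005.

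| q | Pairs lost (8.63 × q) | Observed difference | Exact power |
|---|---|---|---|
| 0 | 0 | 1.60 points | 80.1% |
| 5% | 0.4 | 1.52 points | 76.2% |
| 10% | 0.9 | 1.44 points | 71.8% |
| 20% | 1.7 | 1.27 points | 61.2% |

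**Both exams open to false credit.** Let qB and qC be the chance that B-mode or contrast-enhanced US, having missed the HCC, flags some other lesion as grade 3, independently of each other.
- Contrast only: (0.0165 + 0.0020 qC)(1 − qB)
- B-mode only: (0.0005 + 0.0020 qB)(1 − qC)

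| qB | qC | Observed difference | Exact power |
|---|---|---|---|
| 5% | 5% | 1.52 points | 75.7% |
| 10% | 10% | 1.44 points | 71.0% |
| 20% | 20% | 1.28 points | 60.3% |
| 20% | 5% | 1.24 points | 56.7% |
| 5% | 20% | 1.56 points | 78.3% |

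**Direction.** In points, the observed difference is 1.60 + 0.25 qC − 1.85 qB, where 0.25 = 5.00 − 4.75 and 1.85 = 5.00 − 3.15. It exceeds the true 1.60 only if qC > (1.85/0.25) qB = 7.4 qB. Otherwise the error dilutes the difference.

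**The case against.** The strongest reply is that the rule is deliberate and answers a sensible question. A positive surveillance exam triggers CT or MRI, and if that imaging reveals an early HCC the patient benefits, whichever spot prompted it. The Discussion says the two primary endpoints were chosen to compare screening tests without definitive diagnoses in everyone. That stands: referral of the patient is a defensible target, and this is a design weakness rather than an error or a contradiction. It does not settle the comparison between exams. The stated purpose is the added value of contrast-enhanced US over B-mode, and a wrong-site call credited to the exam that missed the tumour blurs that contrast.

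It is also fair to say that overcalling is penalised overall. At 5% prevalence about 95% of patients have no HCC, and in them each exam with a spurious grade 3 call scores a false referral. The gap is confined to patients with HCC.

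Three stronger readings are tempting, and the documents do not support them.

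- **That the false referral rate is misclassified too.** It is defined as "the proportion of patients having positive US results but confirmed as not having HCC on reference standard procedures". A patient with HCC is outside that definition, so nothing is miscounted under it.
- **That an HCC found much later could turn a false referral into a detection.** CT or MRI for US-positive patients is due "within 60 days after the surveillance US". The remark that "follow up to see the primary end point is still ongoing" reports trial status and sets no rule. A window for pathology may stand in the full protocol.
- **That a clear result would collapse.** A 9–0 split (exact p = 0.004) loses significance at 5–0 (p = 0.0625), but this needs four of nine pairs reclassified, or 44%. That is well outside the 5–20% range used here.

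**Conclusion.** The point holds for the detection rates, early-stage and any-stage. As written, an exam can be credited with an HCC that it did not see, and the per-patient unit does not require this.

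The expected number of patients is small: about 0.4 to 1.7 of 8.6 contrast-only pairs for q between 5% and 20%. With so few discordant pairs, power still falls from 80% to between about 76% and 61%. These figures rest on an assumed q, on the plan's own cell rates, and on reading the planned sensitivities as detection of the tumour itself.

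A reader might infer that the rule is tilted towards contrast-enhanced US. On the plan's rates the reverse is more likely. B-mode misses about 9.7 HCC patients against 1.3, so false credit goes mostly to B-mode and shrinks the difference. Contrast-enhanced US would gain only if its rate of unrelated grade 3 calls in missed-HCC patients were more than about seven times that of B-mode.

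Replacing the primary definition is not warranted, since enrolment has closed and patient-level referral is a defensible target. A matched analysis beside it is.

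**What to change.** Keep the Primary endpoints definitions as the primary analysis. Replace the Reference standards statement that no matching will be done with a pre-specified lesion-matched analysis of the early-stage and any-stage detection rates:

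1. Lock the blinded central CT/MRI reading before any matching starts, so that the panel's blinding is preserved.
2. Credit an exam with a detection only if a grade 3 lesion on its own case report form agrees with a reference HCC by Couinaud segment and by size. Fix the tolerances for both in advance.
3. Keep the patient as the unit, and report the matched and unmatched McNemar results side by side.
4. Tabulate, for each exam, the HCC patients whose grade 3 lesions match no HCC. This supplies the rate that the documents lack.

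The cost is a matching step limited to US-positive patients with confirmed HCC, using data already recorded. It needs no new patients or procedures, and N does not change. The downside is a few borderline segment calls, where the tolerance itself can misclassify. Showing both results makes that visible.
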